## Abstract

**Background:**

Aboriginal and Torres Strait Islander women have a higher prevalence and incidence of obesity and type 2 diabetes than non-Indigenous Australian women. Physical inactivity is a key modifiable risk factor for obesity and evidence shows that even modest reductions in waist circumference (WC) have significant health benefits. Trialing physical activity programs in difficult-to-reach high risk groups, especially urban Indigenous Australians poses distinct implementation challenges.

**Methods/Design:**

The trial objective is to evaluate the effectiveness of a structured 12-week physical activity group program with nutritional advice. The design is a pragmatic randomised controlled trial. This study protocol describes the implementation and evaluation of the program. Participants are randomised into either an intervention or waitlisted group. The waitlisted group have a 12 month waiting period before commencing the 12-week program. Participant data is collected at baseline, 12, 24 and 52 weeks. Participants are Aboriginal and Torres Strait Islander women, aged 18-64 years with a waist circumference greater than 80 centimetres residing in Adelaide. The primary outcome measure is WC change immediately post program from baseline. Secondary outcomes include short term and long term changes in WC, weight, blood pressure, fasting blood glucose, insulin, insulin resistance (calculated HOMA), haemoglobin A1C (HbA1C), triglycerides and C-reactive protein (CRP). Behavioural and psychosocial surveys are administered to assess physical activity, dietary intake and the participant's motivation, self-efficacy and perceived social support for physical activity. Qualitative interviews focusing on participants' motivation, enablers and barriers to healthy eating and physical activity will be undertaken. Implementation fidelity and participation are also assessed.

**Discussion:**

The Aboriginal and Torres Strait Islander Women's Fitness Program (WFP) is designed to provide a rigorous physiological and client-based evaluation of a structured 12-week program aimed to increase metabolic fitness and reduce WC in this high risk population. Evaluation results aim to provide the support necessary to design programs that are accessible, affordable and effective at reducing WC, while also improving the metabolic profile of overweight Aboriginal and Torres Strait Islander women.

**Trial registration:**

Australian New Zealand Clinical Trials Registry ACTRN12610000224022

## Background

The Australian 2004-5 National Health Survey demonstrates that adult overweight and obesity is continuing to rise with 54% of non-Indigenous Australians classified as either overweight or obese compared with 60% of Aboriginal and Torres Strait Islander Australians [1]. There is a disparity among women with 45% of non-Indigenous women classified as overweight or obese compared to 58% of Aboriginal and Torres Strait Islander women. Overweight/obese Aboriginal and Torres Strait Islander women have a lower median age compared to non-Indigenous women (38 vs. 48 years) respectively [1]. Additionally the age-adjusted rate of diabetes for Aboriginal and Torres Strait Islander women are four times the rate for non-Indigenous Australian women [2].

It is established that both waist circumference (WC) and waist to hip ratio are significantly associated with increased risk of cardiovascular disease and that the distribution of body fat is the most important predictive risk factor for the development of type 2 diabetes mellitus (T2DM) [3-6]. The 2000 AusDiab study found that large WCs were associated with undiagnosed T2DM [7]. A 2004 study of Australian Aboriginal people in the Northern Territory found that WC tended to have better sensitivity and specificity in relation to predicting T2DM compared with body mass index (BMI) or waist to hip ratio [8].

Physical activity and diet have been shown to decrease the incidence of T2DM in 'at risk' participants [9] and assist those with T2DM to manage the condition and reduce complications [10,11]. In 2008, a systematic review assessed the effectiveness of randomised controlled clinical interventions designed to reduce the incidence of T2DM in participants at high risk. The review found that interventions combining exercise with diet decreased the incidence of T2DM in participants with impaired glucose tolerance (IGT) or metabolic syndrome [9]. Another review of clinical interventions evaluating the effectiveness of different modes of exercise on glucose control and risk markers for complications in patients with T2DM found small to moderate beneficial effects on glucose control (all modalities), small beneficial effects on some related risk factors for complications of diabetes and further small additional benefits from combining aerobic and resistance exercise [11]. The findings from clinical trials provide support for physical activity and nutrition interventions for people with T2DM or at high risk of developing T2DM.

The evidence supporting the effectiveness of interventions targeting high-risk Aboriginal populations in the community is less robust. It is well-established that implementing rigorously evaluated interventions in community settings is difficult [10,12]. A literature review of these community lifestyle interventions to prevent T2DM was published in 2003 [10]. Of the ten studies conducted in adult populations only one had a randomised design and six did not report any clinical markers in their results. However, many reported an increase in knowledge and physical activity among the intervention groups [10]. Similarly Clifford et al (2011) conducted a literature review of lifestyle interventions targeting Indigenous Australians [12]. Of the twenty studies identified, only four targeted nutrition and physical activity for Indigenous adults, three were conducted in remote areas and one with an urban Indigenous population. All four reported health outcomes and used validated measures; two of the studies were cohorts, one without a control and the other study had a self-selected control group, the third study was a pre/post design without a control group and the forth was a time series design with a randomised control group [12]. One of those reviewed was the Looma Healthy Lifestyle program in Western Australia which focused on education, health promotion and organised physical activities. The program was evaluated using a pre/post design which found initial positive results among a high risk cohort, however weight loss among the participants was not sustained [13]. None of the programs included a structured, evidence-based physical activity program facilitated by qualified and trained instructors. Only one of four studies reported a quantitative measure of program exposure and no study provided a logic model to delineate how the intervention would lead to the primary and secondary outcomes. Without this information it is difficult to rule out implementation failure or theory failure in interpreting the results [12]. Clifford et al (2011) concluded that intervention studies that target healthy lifestyles in Indigenous populations are undertaken infrequently, and are generally of poor methodological quality. Satterfield's (2003) review also concluded that there is a need for community-based interventions to use strong research designs.

Although limited, some small-scale programs implemented in a community setting for high-risk Aboriginal populations have shown encouraging results. In New Zealand, a four month lifestyle intervention was conducted with Maori participants at high risk of developing T2DM [14]. The program consisted of fortnightly clinic visits, nutrition and cooking workshop and individualised exercise programs that prescribed five, 30 minute sessions per week. The program also offered group exercise sessions [15]. The program demonstrated positive results (after the intervention compared to baseline) in most risk markers such as weight loss(3.1 kg), reduction in waist circumference (7.0 cm), body fat (2.0 kg), insulin sensitivity, fasting glucose (0.5 mmol/L) and fasting insulin (5.1 mIU/L)[14].

In 2007, an eight week physical activity program called the Women's Fitness Challenge (WFC) was implemented on Thursday Island in the Torres Strait, which was facilitated by a qualified Torres Strait Islander woman [16]. Participants attended structured aqua aerobics and group circuit class and were assigned pedometers to record their daily steps. Classes included graded exercises to accommodate overweight women, older women and those who had not participated in these types of activities before. However, they were challenging enough for younger and fitter participants with experience in group exercise classes. Participants who attended a final assessment for the program (n = 10) demonstrated a mean reduction in WC of 4.93 cm. There was a strong correlation between the number of self recorded steps (using a pedometer) and reduced WC (R squared = 0.56) and a moderate correlation between the number of classes attended and reduction in WC (R squared = 0.42) [16]. The eight-week WFC informed the development of the Aboriginal and Torres Strait Island Women's Fitness Program.

In summary, evidence for effectiveness of obesity reduction programs implemented in a community setting is mixed. Those reporting success appear to have the following characteristics [17-19]:

• They emphasise physical activity and diet, rather than diet alone

• They accommodate the preferences of participants

• They are conducted in groups

• They have varied and progressive levels and types of activities e.g. combined aerobic and resistance training

In addition, for programs to be sustained, they should be: 1) culturally acceptable; 2) feasible and located close to work or home; 3) easily incorporated into daily schedules, including family activities; and 4) able to show goal attainment which is realistic and appropriate. Compared to the costs to the individual, the health care system and the community, prevention at any level is a highly cost-effective strategy [20].

## Methods/Design

### Study aims

The primary aim of this study is to evaluate whether a structured 12-week physical activity group program with nutritional advice can reduce central obesity (as measured by waist circumference) among Aboriginal and Torres Strait Islander women in an urban setting. The secondary aim is to explore whether WC loss is maintained at 24 and 52 weeks. Additional aims include assessing changes in metabolic profile, participants' quality of life, their dietary and physical activity habits and their motivation, perceived support and self efficacy towards exercise. Qualitative interviews will supply feedback on the program, will help contextualise the quantitative data, explore the participants' motivation, enablers and barriers to healthy eating and physical activity and provide information about any co-interventions, contamination or unexpected/unintended consequences of the program.

### Study design & setting

The effectiveness of the WFP on the WC and metabolic profiles of Aboriginal and Torres Strait Islander women is being assessed using a pragmatic randomised controlled trial. The BMJ 'Clinical Evidence Glossary' defines a pragmatic study as 'an RCT designed to provide results that are directly applicable to normal practice...'[21]. There are many characteristics of a pragmatic RCT that differ from a clinical RCT such as lack of blinding, it may not employ placebos and it may focus on groups with a wide range of diagnoses [22]. The CONSORT guidelines [23] and the recommendations for pragmatic trials have been considered in the projects' design and methodology [24].

It is important that the study maintain methodological rigour whilst being culturally appropriate and ensuring that participants find the protocol acceptable. It was determined by the research team and the local Advisory committee that using traditional 'control groups' would not be acceptable. It was therefore decided that eligible participants would be randomly assigned to either the 'active' group who start the WFP immediately after their baseline assessment or to the 'waitlisted' group, who act as a comparison group for 12 months before 'crossing over' to participate in the program. Each wave of participants was randomised using the PEPI randomisation procedure to create two groups of equal size.

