### Staff

Staffing consists of three chief investigators, an associate investigator, and a Torres Strait Islander and Doctor of Philosophy candidate (KC). The project also employs a project coordinator, qualified fitness instructors, anthropometric assessors (ISAK accredited), a dietician and an experienced Aboriginal interviewer. All staff involved in delivering the project are female, which is essential to ensure cultural safety and sensitivity for our participants.

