**Figure 2 F2:**
[figure not shown]
**Program timeline**. The program timeline is a depiction of the assessment time points (T1-T7) and the 12-week WFP for both the active and waitlisted groups.

Anthropometric assessments are taken by staff accredited by the International Society for the Advancement of Kinanthropometry (ISAK) using the International Standards for Anthropometric Assessment procedures [28]. ISAK assessors have an intra-tester technical error of less than 1.5% and an inter-tester reliability error of less than 2%.

i) Blood pressure and anthropometric assessments:

a. Blood pressure is measured using an Ormon T8 with an upper arm cuff after the participant has been seated for a minimum of 5 minutes. Three readings are taken and the mean of the second and third readings is also recorded.

b. Height is measured using a portable stadiometer (Leicester). The stretched stature is assessed twice to the nearest 0.1 cm; both measures and the average are recorded.

c. Weight is measured using portable digital scales (Tanita BC-532). Participants are asked to empty pockets and remove footwear and weighed wearing light clothing. Two measures and are taken to the nearest 0.1 kg. Both measurements and the average are recorded.

d. Waist and hip circumference are measured over light clothing to the nearest 0.1 cm using a flexible steel measuring tape (Lufkin w606 pm). Both measures and the average are recorded.

ii) Clinical assessments:

Venous blood samples are collected following a minimum 8 hour fast by accredited pathology services in the Adelaide metropolitan area. Pathology results are reported back to participants using the Health Scope Pathology Biochemistry Departments reference ranges [29].

a. Fasting blood glucose is analysed using Hexokinase assay with Siemens Advia 2400.

b. Fasting serum insulin is analysed using Chemiluminescent Immunoassay with Siemens Advia 2400.

c. HbA1C is analysed using Immunoturbidimetry assay with Roche Integra 800.

d. Total cholesterol, high-density lipoprotein (HDL), low-density lipoprotein (LDL) and triglycerides were analysed using Chemiluminescent Immunoassay with Siemens Advia 2400. LDL/HDL and Cholesterol/HDL ratios are also calculated.

e. C-reactive protein (CRP) is analysed using Immunoturbidimetry assay with Siemens Advia 2400.

f. Homeostatic Model Assessment (HOMA) is calculated using the formula;

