### Statistical Analysis

The active and waitlisted groups will first be compared at baseline (T1). Continuous variables will be compared using Student's T tests. Categorical variables will be compared using Chi-squared tests. No attempt will be made to adjust for clustering. Analyses will be undertaken using SPSS 16 and Stata 10.

The primary outcome measure (change in waist circumference between T1 and T2) will be compared between groups at T2 both crude (unadjusted) and adjusted for baseline waist circumference using analysis of covariance. Further analyses will adjust for other potentially confounding variables, such as age, number of children, education, employment status, household income and illness/disease.

Change in waist circumference between T1 and T3, and between T1 and T4 will be compared between groups both crude (unadjusted) and adjusted for baseline waist circumference. Further analyses will adjust for other confounding variables. The additional anthropometric and clinical assessments will be analysed in the same way to compare the active group with the waitlisted group at each time point.

Changes in major outcome measures over time will be explored using linear mixed modelling. Predictors of WC change, and possibly other measures, will be explored within the active group to detect any trends that may suggest barriers or enablers to positive change.

Further regression analyses will explore any association of psychological and behavioural variables with reduction in waist circumference.

The waitlisted participants will appear in the data set more than once as they 'cross over' to join the active group after their 12 months in the waitlisted group. This will be allowed for in the analysis using linear mixed modelling.

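### No masking is set for the assessors who read the tape-measured primary outcome, so waist change is open to observer bias that the stated safeguards do not remove

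*Protocol article*

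**What the plan says.** **Blinding.** The only remark is in Study design & setting, in the paragraph that labels this trial pragmatic, which says that there are many "characteristics of a pragmatic RCT that differ from a clinical RCT such as lack of blinding". The same sentence mentions the possible absence of placebos and a wide range of diagnoses. No section names a masked role.

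**Primary outcome.** Statistical Analysis states: "The primary outcome measure (change in waist circumference between T1 and T2) will be compared between groups at T2". The comparison is made both crude and adjusted for baseline waist by analysis of covariance.

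**Measurement.** The measurement text after Figure 2 states: "Waist and hip circumference are measured over light clothing to the nearest 0.1 cm using a flexible steel measuring tape". Both readings and their average are recorded. The measuring staff are ISAK-accredited and follow the international standard, with stated error limits of 1.5% within and 2% between assessors.

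**Staffing.** The Staff section lists "qualified fitness instructors, anthropometric assessors (ISAK accredited), a dietician" as roles alongside a project coordinator and an interviewer.

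**The concern.** Women cannot be masked to whether they attend exercise classes. That does not carry over to the person holding the tape: a pragmatic question about normal practice does not need the outcome reader to know the group. Waist over clothing depends on where the tape is placed and how tightly it is drawn, so there is room for judgement. An assessor who knows that a woman has just finished the program may read slightly low without intending to.

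At stake is the single primary outcome. A shift of this kind adds directly to the estimated program effect, and the collected data cannot separate the two. The exposure lies mainly in the follow-up readings. Eligibility depends on the baseline waist, so T1 presumably precedes allocation, although the article does not state the order outright. The laboratory outcomes are much less exposed.

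**Working it through.** **1. Inputs (all from Sample Size Estimation).** Target difference 4 cm; SD 3.47 cm; two-sided t-test at 0.05; 80% power; 13 per group; loss to follow-up of nearly 60% (pilot: 14 of 24, or 58.3%); 40 enrolled per group.

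**2. The plan's own figure.** With 13 per group, the noncentrality is 4 / (3.47 × √(2/13)) = 4 / 1.361 = 2.94 on 24 degrees of freedom, and power is 80.5%. Solving for 80% power gives n = 12.85, so 13 per group is reproduced. For dropout, 13 / (1 − 14/24) = 31.2, so 32 is reproduced too.

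**3. Expected completers.** 40 × (1 − 0.60) = 16 per group.

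**4. Do the stated safeguards remove a group-dependent shift?**
- *Accreditation and standard procedure:* these limit random error within and between assessors. They do not address knowledge of group.
- *Averaging readings:* if each reading is shifted by b, the average is also shifted by b.
- *Baseline adjustment:* the adjusted difference is (mean T2 active − mean T2 waitlisted) − β × (mean T1 active − mean T1 waitlisted). A shift b that enters only at T2 in one arm changes the first bracket by b and leaves the second alone. The estimate moves by b whatever β is. The crude change score is the case β = 1.

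**5. Size, as an assumed range.** The documents give no value for b, so three values are taken: 0.5, 1.0 and 1.8 cm. With no true effect, SD 3.47 and 16 per group, the standard error is 3.47 × √(2/16) = 1.227 cm. The noncentrality is b / 1.227 on 30 degrees of freedom, and the two-sided rejection rate comes from the noncentral t distribution.

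| Assumed differential reading b | Share of the 4 cm target | Noncentrality | Rejection rate with no true effect |
|---|---|---|---|
| 0 | 0% | 0 | 5% |
| 0.5 cm | 12.5% | 0.41 | 7% (6.8%) |
| 1.0 cm | 25% | 0.82 | 12% (12.4%) |
| 1.8 cm | 45% | 1.47 | 30% (29.5%) |

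Masking would not change the sample size; it bears on the validity of the estimate.

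**The case against.** The strongest reply is that this is silence in a condensed article. The sentence on blinding describes pragmatic trials in general, and the same section says that CONSORT and the recommendations for pragmatic trials were considered. A fuller protocol might set masking. Part of this stands: a reader might infer that the protocol declares its assessors unmasked, or defends leaving them so, and the text does neither. It does not dispose of the point. The article takes up blinding itself, and its one remark points towards none. It also describes the waist measurement in detail without restricting the assessor's knowledge of group.

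Four further inferences are tempting and are not supported:
- *That the assessors are independent of the classes, so masking costs nothing.* Staff lists a distinct role and does not say that assessors stay out of delivery. The Program section has project staff coordinating and supervising classes, and Process evaluation places a project officer at each session. If people hold more than one role, masking may be harder to arrange.
- *That the 1.5% and 2% limits give the size of the bias.* They are upper limits on random measurement error. The largest assumed value is close to 2% of the pilot baseline mean (0.02 × 91 = 1.82 cm), but that serves only for scale and is not evidence of a shift between arms.
- *That the inflation should be computed at 40 completers per arm, where it would be larger.* Forty is the enrolled number, and the plan itself expects nearly 60% to be lost.
- *That changing assessor between visits belongs to the same problem because it costs power.* That is random error, which masking does not address.

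It is also fair that the three intakes (April 2010 to March 2011) are described in the past tense, so some T2 readings may already have been taken. That limits what can be changed, but not what should be reported.

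**Conclusion.** The concern holds in this form: the plan sets no masking for those who read a manual primary outcome, its sole comment on blinding names the absence of blinding as a characteristic of pragmatic trials, and neither the measurement procedure nor the planned analysis removes a group-dependent shift at T2. It is a weakness in the design as described, and it does not show that bias occurred.

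The range of about 7% to 30% false positives against a nominal 5% rests on four assumptions: a differential reading of 0.5 to 1.8 cm, which no document supplies; no true effect; the plan's SD of 3.47 cm applied to the change in waist; and 16 completers per arm. At the low end the effect is small. At the high end it would seriously undermine a positive primary result.

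**What to change.** State in the methods that:
- the T2, T3 and T4 anthropometric readings are taken by the existing ISAK assessors, without access to the allocation or to the woman's earlier readings;
- these assessors are rostered away from class delivery where staffing allows;
- women are asked before each assessment not to disclose their group;
- the assessor's identity and any unmasking are recorded at each visit and reported.

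For visits already completed without masking, the report should say so and list it as a limitation of the primary result.

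The cost is some rostering effort and a short instruction to assessors and participants. Whether the present staff suffice depends on how far roles overlap, which the article does not say. Masking will sometimes fail, because women may mention the classes, and the recorded unmasking lets readers judge how often.

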### Recruitment

Participants were recruited in three intakes (April 2010, September 2010 and March 2011). The first two programs were delivered at the City East Campus of the University of South Australia, Adelaide. The third program was based in an outer suburb (30 km from the Adelaide CBD) with a high proportion of Aboriginal residents.

Project staff visited local Aboriginal and Torres Strait Islander organisations, health centres and community groups to inform them of the project and ask them to display posters and distribute brochures. Several information sessions were held during each recruitment phase to allow potential participants to meet project staff and become fully informed on the project before formally registering to participate. A project flier distributed via e-mail proved to be an effective way of recruiting participants. In addition social networks were also an effective recruitment tool.

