### Sample Size Estimation

The primary outcome for the study is to assess if waist circumference reduction immediately after the program compared to baseline will be greater in the active group than the waitlisted group. Feasibility of this program has been demonstrated in a pilot program (WFC) in 2007. The eight week pilot program enrolled 24 women, 10 of whom had baseline and follow-up assessments (there was no comparison group). Those assessed lost a mean of 4.93 cm (95% confidence interval 2.44-7.41, SD = 3.47 p = 0.002) of WC from baseline (mean at baseline 91 cm to 86 cm at 8 weeks). The degree of waist loss was proportional to adherence to the program (r = 0.647) [39]. Therefore we assume an expected program effect of a reduction of 5 cm in WC after 12 weeks in the active group. The waitlisted group receive a modest intervention and are not strictly a control group therefore we estimate that the waitlisted group may have a WC reduction of 1 cm over the same time period equating to a 4 cm difference between groups. A sample size of 13 per group would have 80% power to detect a difference in waist circumference of 4 cm assuming a standard deviation of waist circumference of 3.47 cm and using a two sided independent samples t-test with a 0.05 level of significance. Experience from the WFC however predicts that nearly 60% of participants will be lost to follow-up which would increase the group size to 32. This calculation assumes that the participants are independent however many women will be colleagues or family members so we have increased our sample size estimation to 40 participants per group.

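### Randomisation was done within three intake waves, but the stated primary model leaves wave out: a slight, conservative precision error, and a conditional route to bias at the expected loss

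*Protocol article*

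**What the plan says.** **Allocation.** Study design & setting: "Each wave of participants was randomised using the PEPI randomisation procedure to create two groups of equal size". Wave is therefore a stratification factor by design.

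**What the waves were.** Recruitment lists three intakes: April 2010, September 2010 and March 2011. On delivery it says "The first two programs were delivered at the City East Campus of the University of South Australia, Adelaide" and then "The third program was based in an outer suburb (30 km from the Adelaide CBD) with a high proportion of Aboriginal residents". I take each intake to be one wave.

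**Analysis.** Statistical Analysis compares change in waist circumference from T1 to T2 crudely, and then "adjusted for baseline waist circumference using analysis of covariance". Further analyses may adjust for other variables. Age, number of children, education, employment, income and illness are given as examples, so the list is open. Mixed models are described for change over time and for waitlisted women who enter the data twice. Wave, intake and site are not named in any of these.

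**Size and loss.** Sample Size Estimation: "A sample size of 13 per group would have 80% power to detect a difference in waist circumference of 4 cm". The SD behind this is 3.47 cm. Nearly 60% loss is expected. The planned size is 40 per group.

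**The concern.** When allocation is balanced within strata, differences between strata cancel out of the treatment contrast. A model without the strata still counts those differences as residual noise. It then reports a standard error larger than the real sampling variation, and the precision that the design gained is not used.

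That protection covers women as randomised. It carries over to women as analysed only if the ratio of retained active to retained waitlisted women stays about the same in every wave. At the planning loss about 16 per arm remain, or roughly five per arm per wave, so an uneven ratio is easy to imagine. Active women had classes to attend at their wave's site, while waitlisted women did not start the programme for 12 months. If waves also differ in mean waist change, an uneven ratio carries part of that difference into the estimated programme effect.

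**Working it through.** **Inputs from the protocol article.** Target difference 4 cm; SD 3.47 cm (variance 12.04); two-sided 5% level; 13 per group before loss; nearly 60% loss; 40 per group planned; three waves, equal arms in each.

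**Assumptions.** The article gives no wave effect and no retention by wave. I take waves of nearly equal size (14/13/13 per arm), 3.47 cm as the SD of waist change within wave, and a shift *d* of 0–3 cm in the third wave's mean change, the same in both arms. The simulations used 5,000 runs per setting and a treatment term with or without wave indicators. Baseline waist circumference was not modelled.

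**1. The plan's own figure.** The two-sample t-test has power 77.0% at 12 per group and 80.5% at 13, so 13 reproduces. Loss: 13/0.40 = 32.5; at the pilot's loss of 14/24 = 58.3%, 13/(10/24) = 31.2, which rounds up to the stated 32. Of 40 per arm, 40 × 0.40 = 16 remain.

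**2. Standard error with full retention.** A third of women shifted by *d* gives a between-wave variance of (1/3)(2/3)*d*² = (2/9)*d*². The inflation from leaving wave out is √(1 + (2/9)*d*²/12.04).

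| *d* (cm) | (2/9)*d*² | Inflation |
|---|---|---|
| 1 | 0.222 | 0.9% |
| 2 | 0.889 | 3.6% |
| 3 | 2.000 | 8.0% |

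At 3 cm the simulated type I error is 3.6% without wave and 5.3% with it.

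**3. Standard error at 40% retention, the same in every cell.** Random loss makes the arms uneven within wave, so the real sampling variation also rises and the gap narrows. At 3 cm the mean reported standard error is 1.33 cm against an actual sampling SD of 1.30 cm (1.33/1.30 = 1.02). Type I error is 4.2%. Power for 4 cm is 82.3% without wave and 85.0% with it. Even at 3.7 cm the mean reported standard error is only about 3% too large. There is no bias.

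**4. Bias when the retained ratio differs by wave.** Bias = *d* × (share of retained active women in wave 3 − share of retained waitlisted women in wave 3). Both patterns below keep 40% overall in each arm.

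- *Severe:* active 50/50/20%, waitlist 30/30/60%. Shares 0.2/1.2 = 1/6 and 0.6/1.2 = 1/2; difference −1/3.
- *Milder:* active 50/50/20%, waitlist 40/40/40%. Shares 1/6 and 1/3; difference −1/6.

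| *d* (cm) | Bias, severe (cm) | Type I error, severe | 95% CI coverage, severe | Bias, milder (cm) |
|---|---|---|---|---|
| 1 | 0.33 | 5.5% | 94% | 0.17 |
| 2 | 0.67 | 7.5% | 92% | 0.33 |
| 3 | 1.00 | 10.7% | 89% | 0.50 |

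Bias is shown in absolute size; its direction depends on which arm loses more women in which wave. With wave in the model, bias under the severe pattern is about zero and type I error about 5%. If the arms differ in retention but equally in every wave (60% against 30%), the shares are the same and the bias through wave is zero.

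**5. Price of the term if wave has no effect.** At 40% equal retention the sampling SD goes from 1.27 to 1.30 cm (1.30/1.27 = 1.02). Under the severe pattern it goes from 1.26 to 1.38 cm (1.38/1.26 = 1.10), and power from 87.3% to 80.9%.

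**The case against.** The best case against is that this is a detail for the statistical analysis plan. The article is condensed, its further-covariate list is open, and the terms of the mixed models are not itemised. This stands for the secondary models, where wave is unnamed and not excluded. It does not stand for the primary comparison, whose adjustment is stated: none, or baseline waist circumference.

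A reader might infer several stronger things that the documents do not support:

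- *That ignoring the strata makes the intervals too narrow.* The direction is the opposite. With even retention they are slightly too wide.
- *That the precision loss is 5–12%.* This corresponds to wave explaining 10% or 20% of the variance. Solving (2/9)*d*² = 12.04/9 and 12.04/4 gives shifts of about 2.5 and 3.7 cm, the second nearly the whole target effect, and nearly full retention is needed as well. At the expected loss the figure is about 0–3%.
- *That the loss makes the result confounded.* Loss alone does not. Both a wave difference in mean change and an uneven retained ratio are needed, and the article reports neither. The loss figure itself is a planning value from a pilot of 24 women.
- *That every wave differs in season and site.* Waves 1 and 2 share a site, and April and March fall at a similar time of year.

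One further objection stands in full. Waitlisted women do not take the programme for 12 months, so an effect of delivery site would act mainly in the active arm. That is a wave-by-arm interaction, which an additive wave term does not represent.

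**Conclusion.** The point holds in a limited form. The trial randomised within wave, and the stated primary model does not include wave. With little loss the consequence is minor and conservative: a standard error about 1–8% too large for assumed shifts of 1–3 cm. At 40% retention it is about 0–3%, with type I error of about 4–5%.

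The stronger reason to act is the expected loss. Where waves differ in mean waist change and the retained arm ratio varies between them, the bias is about 0.3–1.0 cm against 4 cm under a deliberately severe pattern, and about 0.2–0.5 cm under a milder one. These sizes rest on assumed wave shifts and retention patterns. They show what could happen and are not estimates for this trial. The change is worth making because it is cheap and matches the design, not because the plan is shown to be invalid.

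**What to change.** Add wave, as a fixed effect with three levels, beside baseline waist circumference in the primary analysis of covariance. Add it also to the other between-group models and to the mixed models. Each woman's intake is known, so no new data are needed.

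The cost is 2 degrees of freedom. With 32 women retained, the residual falls from 32 − 3 = 29 to 27. If wave has no effect, precision falls by about 2% at even 40% retention, and by more if retention is very uneven (about 10% under the severe pattern), which is the price of protection against the bias.

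The term does not correct other informative dropout, clustering by family, workplace or exercise class, or a programme effect that differs between waves.
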